### Outcome Measures

#### Primary Outcomes

The primary outcomes of this study are the feasibility of the proposed protocol, the dose of unsupervised robot-assisted therapy performed by participants, and the difference between usability and user experience between the phases where a therapist is present (ie, supervised and minimally supervised phases) and the unsupervised phase.

Feasibility is measured as the number of patients who could transition to the unsupervised phase out of the total number of tested patients, attendance during the unsupervised phase, and safety of use. Attendance is defined as the percentage of days out of the total number of offered days where the patient trains with the device at least once, while safety is defined as the number of adverse events and device deficiencies throughout the entire protocol.

The different metrics used to characterize therapy dose are therapy duration in minutes, number of task repetitions (ie, the number of target movements performed), and percentage change in physical therapy time with respect to the conventional therapy program. Total conventional physical therapy time is estimated from the sum of the duration in minutes of the physiotherapy (without differentiating between upper limb and lower limb) and occupational therapy sessions regularly performed by each patient at the clinic.

Platform usability is assessed with the System Usability Scale [29], the raw Task Load Index [30], and the Post-Study System Usability Questionnaire [31]. User experience during robot-assisted therapy is assessed with the Net Promoter Score [32] and the Customer Satisfaction Score, as well as by evaluating the reasons (if any) for not attending the therapy sessions with the device.

The results of the checklist used to define which patient can proceed to unsupervised therapy are also used to identify specific aspects of the platform that might need to be further improved.

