**Results:**

As of April 2023, 13 patients were recruited and completed the protocol, with no reported adverse events.

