**Figure 2 figure2:**
[figure not shown]
Design of the interventional study for each of the study participants. All participants undergo a screening visit, baseline assessments, 1 week of supervised therapy, and 1 week of minimally supervised therapy. After the first week of minimally supervised therapy, the therapist checks whether the patient properly learned how to use the technology and is ready for unsupervised training. If yes, the patient proceeds to 2 weeks of unsupervised use. If no, an additional week of minimally supervised therapy is performed. At the end of this second week, the therapist checks again whether the patient can train independently. If yes, the patient proceeds to 1 week of unsupervised therapy. If no, an additional week of minimally supervised therapy is performed. In total, each patient performs 4 weeks of technology-assisted rehabilitation. At the end of the protocol, the clinical and robotic assessments as well as the evaluation of the user experience and usability are repeated for all patients.

**Table 1 table1:** Data collected and procedures (marked with an “X”) performed at each time point of the clinical trial, with primary (PO) and secondary (SO) outcomes indicated. Day 0 corresponds to the first supervised robot-assisted therapy session. The time range indicates how far a procedure can be advanced (–) or postponed (+) for organizational reasons from the precise time point at which it should be performed.

		Screening visit	Baseline clinical assessment	Baseline robotic assessment	Robot-assisted therapy sessions		Usability evaluation 1	Robot-assisted therapy sessions		Final clinical assessment	Final robotic assessment	Usability evaluation 2
Time point		Day –2	Day –1	Day –1	Day 0-6	Day 7-13	Day 13	Day 14-20	Day 21-27	Day 27	Day 27	Day 27
Time range (days)		–4 to +1	±2	±1	—^a^	—	±2	—	—	±2	±2	±2

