Before starting the intervention, patients undergo a screening visit with a medical doctor at which the eligibility criteria are checked and demographic and medical data relevant for patient characterization are collected. At the beginning and end of the study, patients undergo a visit with an experienced therapist where clinical assessments are performed to characterize upper limb sensorimotor deficits. Before the first robot-assisted therapy session and at the end of the study, robotic assessments are performed. The baseline robotic assessments are used to tailor the initial difficulty level of the therapy exercises. As robotic therapy is an addition to conventional therapy and this protocol does not comprise a control group, functional recovery is not used to evaluate the efficacy of unsupervised robot-assisted therapy, as it is not possible to infer how much of the recovery is due solely to the addition of robotic therapy, but rather to investigate the possible relation of different impairment profiles on the observed increase in therapy dose.

During the first week of intervention (ie, the supervised phase), a therapist familiarizes the participants with the therapy platform and teaches them how to perform the therapy exercises. During the second week (ie, the minimally supervised phase), participants try to perform the therapy exercises with the device by themselves. A therapist is still present in the room but intervenes only upon request or if deemed to be needed. The first 2 phases consist of 5 sessions of about 45 minutes each, performed on consecutive days (weekends excluded). These sessions are an addition to standard therapy. Therefore, during the study, participants are allowed to fully follow the conventional interdisciplinary rehabilitation program provided by the clinic.

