During the last session of the minimally supervised phase, a checklist (Multimedia Appendix 1) is used by the therapist to record whether participants learned how to correctly perform each assigned therapy exercise. The checklist is also used to assess the patient’s functional independence in ambulation and in positioning in front of the device and to decide if the patient meets the requirements to train with the technology in a safe and effective way without supervision. If the requirements are met, the participant can proceed to the unsupervised phase, which lasts for 2 weeks. During the unsupervised phase, patients can independently exercise with the rehabilitation platform during their free time, during dedicated sessions indicated on their therapy schedule, as well as after 5 PM and during the weekend. Specific guidelines on how much to train are not provided. Even though a possible time to train with the device is suggested on the patient’s daily therapy schedule during weekdays, patients are clearly told that they do not necessarily need to attend the session but can rather freely decide when to seek additional therapy within the offered slots or whether to go at all (ie, as a way to simulate home settings).

If, at the end of the first week of minimally supervised therapy, the patients do not meet the requirements to transition to the unsupervised phase, they continue with minimally supervised therapy for an additional week. At the end of the second minimally supervised week, the checklist is performed again. If the patients are now ready for unsupervised training, they can proceed to 1 week of unsupervised therapy; if they are not ready, they undergo a third week of minimally supervised sessions (Figure 2).

During the entire study, the device is placed in an open-access room and an emergency call system is available next to it. Trained personnel of the clinic turn on the device in the morning and turn it off in the evening. If needed, patients are taken to the device by the personnel of the clinic responsible for patient transportation. The personnel might also help patients to position themselves in the correct way in front of the device but do not help with placing the patient’s hand on the handles or operating the device.

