The usability of the platform and user experience during robot-assisted therapy is rated a first time at the end of the first week of minimally supervised therapy and a second time at the end of the study. The difference in the ratings between the 2 time points is used to investigate the effect of unsupervised training (ie, of the therapist’s absence) on the perceived usability of the therapy platform and on the user experience during technology-assisted rehabilitation.

Adverse events and device deficiencies are monitored throughout the whole study protocol. The intervention can be discontinued after consultation with medical doctors and therapists or if the participant decides to quit.

For each patient, attendance to the robot-assisted therapy sessions is registered. As attendance to robot-assisted therapy is one of the study outcomes, strategies to increase adherence are not implemented. Reasons for nonattendance are registered a posteriori for each missed supervised or minimally supervised session as well as if patients train for less than 50% of the possible days (ie, less than 7 of 14 days when the patient undergoes 2 weeks of unsupervised therapy or less than 4 of 7 days in cases where the patient undergoes only 1 week of independent training) during the unsupervised phase.

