### Monitoring

Monitoring is performed by a study nurse employed at the sponsor institution. An initiation visit on-site is performed to check the suitability of the infrastructure and staff. Routine monitoring is then performed through on-site or web-based visits depending on the needs of the investigators (eg, on request or for safety reasons). A close-out visit is performed after the completion of the study. Interim analysis is not foreseen.

Observed or spontaneously reported adverse events are collected and assessed by one of the medical doctors involved in the clinical study and recorded on the CRF. Adverse events are then reported in the annual safety report and final report. Serious adverse events are reported to the ethics committee and to the competent authority within 7 days.

Auditing may be conducted at any time by the ethics committee or the competent authority, both independent from the sponsor and investigator. The study documentation, CRF, and informed consent are accessible for auditing.

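### The primary safety measure is one event count over the whole protocol, so it cannot separate unsupervised use from therapist-attended use

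*Protocol article*

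**What the plan says.** The Primary Outcomes section measures feasibility by three things: the number of patients who transition, "attendance during the unsupervised phase, and safety of use". It then fixes the last of these: "safety is defined as the number of adverse events and device deficiencies throughout the entire protocol". No denominator and no split by supervision phase are given.

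The Intervention section agrees on the period covered: "Adverse events and device deficiencies are monitored throughout the whole study protocol". Table 1 marks adverse events in every column. It marks device deficiencies in the robotic assessment and therapy columns only. Its caption describes the table as showing procedures "with primary (PO) and secondary (SO) outcomes indicated", yet both rows carry a plain X and not the primary-outcome mark.

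On collection, the Monitoring section states: "Observed or spontaneously reported adverse events are collected and assessed by one of the medical doctors involved in the clinical study". Supervision differs by phase. In the minimally supervised week, "A therapist is still present in the room but intervenes only upon request or if deemed to be needed". In the unsupervised phase, patients may train alone in their free time, "during dedicated sessions indicated on their therapy schedule, as well as after 5 PM and during the weekend".

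The abstract's Results paragraph gives one pooled statement: "13 patients were recruited and completed the protocol, with no reported adverse events".

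**The concern.** The first aim in the Introduction is the feasibility of unsupervised robot-assisted therapy and of the transition to it. The Discussion expects the training procedure to lower the risk of adverse events when patients train alone, and treats success in the clinic as the step before home use. The safety result that bears on this is what happens while nobody supervises.

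The stated measure cannot supply that result. It puts the attended weeks and the unsupervised weeks into one number. The other on-device measures are tied to a phase or compared between phases: attendance and dose belong to the unsupervised phase, and usability, intensity, performance and the effective-time ratio are contrasted by level of supervision. Safety is the exception.

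Two consequences follow. An adverse event or device deficiency in an attended session counts the same as one that occurs when the patient is alone. And a total of zero invites the reader to credit the whole observation period to unsupervised use, when only part of it was unsupervised.

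**Working it through.** **The plan's own figure.** Sample Size starts from 10 patients and allows for about 20% dropout: 10 / (1 − 0.20) = 12.5, rounded up to 13. This reproduces. The article states no precision, threshold or confidence level for safety, so there is no safety figure to reproduce. The 95% limits below are my choice, for illustration.

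**Inputs.** 13 patients (Sample Size). Intervention from Day 0 to Day 27, that is 28 days (Table 1). Unsupervised time of two weeks, one week or none, depending on the checklist (Intervention; Figure 2 caption). The share of patients on each path is not given and is assumed.

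**Exposure in calendar patient-days.**
- Whole intervention: 13 × 28 = 364.
- All transition after week 2: 13 × 14 = 182 unsupervised days, 182/364 = 50%.
- All transition after week 3: 13 × 7 = 91 unsupervised days, 91/364 = 25%.

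Patients who never transition add nothing, so the share could fall below 25%. Screening and baseline days are left out; including them would enlarge only the pooled denominator.

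**Upper limit for a rate with zero events** (constant Poisson rate, one-sided 95%): −ln(0.05) / days, with −ln(0.05) = 2.996.
- Pooled: 2.996 / 364 = 0.82 per 100 patient-days.
- Unsupervised, 182 days: 2.996 / 182 = 1.65 per 100.
- Unsupervised, 91 days: 2.996 / 91 = 3.29 per 100.

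The pooled zero therefore looks 364/182 = 2 to 364/91 = 4 times as precise as the unsupervised data allow in these two scenarios.

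**Upper limit per patient with zero events** (exact, one-sided 95%): 1 − 0.05^(1/n).
- n = 13 entering the unsupervised phase: 20.6%.
- n = 10 entering: 25.9%.

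If all 13 enter, this limit is the same with or without pooling. It reflects the small sample. The effect of pooling shows in the exposure-based limits, and per patient only when some patients never enter.

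**Why calendar columns are not enough.** Table 1 allows minimally supervised therapy in Days 14-20 and 21-27 for patients who are not ready. Tabulating by these columns would put attended use under the unsupervised heading.

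**Device time.** The two attended weeks schedule 2 × 5 sessions of about 45 minutes, or 450 minutes per patient. No training amount is set for the unsupervised phase, so the device-hour ratio cannot be worked out from the article. The robot logs log-in and log-out times and session duration (Table 1, footnote p), so the investigators can compute it.

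**The case against.** The strongest reply is that the primary outcome is the feasibility of the proposed protocol as a whole, and a whole-protocol count suits that target. This stands as a reason to keep the count. It does not make the count informative about unsupervised use, which the first aim names.

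A second reply is that recording is scheduled in every period and tabulation is normally left to an analysis plan. Events can probably be assigned to a phase, and the definition does not forbid a breakdown. But the article does not merely omit a detail: it states what the safety measure is, and that stated measure has no phase and no exposure.

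Several stronger readings are tempting and are not supported:
- A reader might infer that only volunteered events are recorded when patients train alone, so that the unsupervised count is biased toward zero. One collection rule applies to all phases. Participants are inpatients who continue conventional therapy, the room is open-access, and an emergency call system is beside the device. What is lost is the therapist's direct view during device use. Lower capture is plausible, but no capture rate is given and no size can be put on it.
- A reader might say attended use dilutes the count. A count has no denominator, and adding periods can only raise it. The issue is separation and apparent precision.
- A reader might take the 20.6% limit as the cost of pooling. It is the cost of having 13 patients, and the sample is openly justified as a feasibility sample.
- A reader might ask for an added safety question to patients. The Results section says all 13 had completed, so this is no longer possible in this study.

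**Conclusion.** The point holds for the outcome definition. The safety component of primary feasibility, as written, cannot separate adverse events or device deficiencies under unsupervised use from those in attended periods. A pooled zero overstates precision for unsupervised use by a factor of 2 to 4 in the scenarios shown: 0.82 against 1.65 to 3.29 per 100 patient-days. These figures assume a constant rate, zero events, no dropout, and uniform transition after week 2 or week 3. They use calendar days because device hours are not published.

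The abstract reports no adverse events, so a split would leave that count at zero in every phase; what changes is the exposure behind it. The abstract is silent on device deficiencies, where a split could change the picture. Differential under-ascertainment remains an inference to be stated as a limitation. Even a phase-specific zero in at most 13 patients would not demonstrate safety.

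**What to change.** Keep the whole-protocol count and add the following:

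1. Tabulate adverse events and device deficiencies by the supervision actually in force at onset (supervised, minimally supervised, unsupervised), not by calendar column.
2. Give each phase its denominators: patients who entered it and logged device hours.
3. For the unsupervised phase, report an exact 95% upper limit based on the patients who entered it, and state whether it is one- or two-sided.
4. Word a zero as none reported, as the abstract already does for the pooled result. Add as a limitation that events were collected when observed or volunteered and that the therapist's direct observation was absent in this phase, so some may have been missed.

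The device logs and event records are already scheduled, and the Results section describes analysis as ongoing. Provided event dates are recorded, which the article does not say explicitly, no new data are needed. The cost is a small amount of re-tabulation and a safety statement that looks less favourable.

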#### Secondary Outcomes

The difference in intensity (ie, number of task repetitions per minute) and task performance during supervised or minimally supervised therapy and unsupervised therapy is used to evaluate if the content of the therapy varies when the therapist is no longer present. A task repetition corresponds to the target action that the patient must perform in a given exercise (eg, a movement or combination of movements, such as one opening and closing of the hand or interacting with one virtual object rendered by the robot). A third metric to evaluate the difference in therapy content is the ratio of effective therapy time (ie, net therapy time without breaks) to total duration of a therapy session during supervised or minimally supervised therapy and unsupervised therapy.

Functional recovery, assessed as the difference between the baseline and final scores in the clinical and robotic assessments, is another secondary outcome. Clinical assessments comprise the Fugl-Meyer Assessment for upper extremities [33], ABILHAND [34], the Box and Block Test [35], the Motor Evaluation Scale for Upper Extremities in Stroke Patients [36], and the modified Ashworth Scale [20]. Robotic assessments comprise active range of motion, hand proprioception, and haptic perception (A1-A3 in [25]).

The scores of the cognitive assessments performed during the screening visit (Goodglass-Kaplan scale and levels of cognitive functioning-revised) are used to gain more insights into the effect of cognitive function on the ability to transition to the unsupervised phase.

Other parameters possibly influencing therapy dose or attendance are also evaluated. These comprise age, baseline assessment scores, functional recovery, the number of total conventional therapy sessions, and functional independence and mobility, as assessed with the Barthel index [37] and custom questions every time the checklist is performed (ie, at the end of each week of minimally supervised therapy).

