**Figure 1 figure1:**
[figure not shown]
A patient with stroke performing an exercise with the ReHapticKnob. During a therapy session with the device (left), users first log in to their personal therapy account with a fingerprint reader; then, when performing the exercises, they place their fingers on the handles and interact with the virtual reality interface by using a colored pushbutton keyboard. As the exercises implemented on the ReHapticKnob require the user to solve tasks by relying on the sensorimotor information coming from the impaired limb and not on visual information, view of the impaired hand is blocked with a hand cover. The ReHapticKnob allows for grasping (top right) and forearm pronosupination (bottom right) movements.

The rehabilitation exercises implemented on the RHK follow the neurocognitive therapy approach [22-24] and promote motor learning by focusing on sensorimotor integration, as they require patients to use kinesthetic and proprioceptive information from their impaired upper limb and cognitively process it to solve the therapy tasks in the correct way. Assessment-driven exercises ensure an optimal difficulty level from the beginning while ensuring dynamic difficulty adaptation based on the user’s performance [25]. Therapy with the RHK was previously shown to be as efficient as dose-matched conventional therapy [26] when performed in supervised settings.

To make the device suitable for unsupervised use, design changes, such as the implementation of a new graphical user interface and pushbutton keyboard to allow direct interaction between the user and the device, were implemented and tested in a previous usability study [24]. Building on that work, the usability of the platform was further improved by implementing minor graphical changes and audio instructions for the exercises. Furthermore, the platform was improved by integrating clinically inspired algorithms to automatically monitor, control, and adapt therapy in a personalized way [27,28]. This set of algorithms was evaluated in a pilot study with 5 patients with subacute stroke, demonstrating its ability to guide them through several therapy sessions with the RHK and to automatically adapt the difficulty level of the exercises to keep therapy challenging.

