**Others**												
	Robotic therapy data^p^	—	—	—	PO	PO	—	PO	PO	—	—	—
	Conventional therapy data^q^	—	—	—	X	X	—	X	X	—	—	—
	Adverse events	X	X	X	X	X	X	X	X	X	X	X
	Device deficiencies	—	—	X	X	X	—	X	X	—	X	—

^a^Not applicable.

^b^Demographics include gender, age, year of birth, and hand dominance.

^c^Medical data include stroke onset, lesion type and side, and impaired hand.

^d^VASp: visual analogue scale for pain.

^e^BBT: Box and Blocks Test.

^f^MESUPES: Motor Evaluation Scale for Upper Extremities in Stroke Patients.

^g^FMA-UE: Fugl-Meyer Assessment for upper extremities.

^h^mAS: modified Ashworth Scale.

^i^(X): Performed only for patients who are not ready to train without supervision. These will continue with 5 additional minimally supervised therapy sessions. In this case, the checklist is repeated during the fifth session.

^j^SUS: System Usability Scale.

^k^PSSUQ: Post-Study System Usability Questionnaire.

^l^TLX: raw Task Load Index.

^m^NPS: Net Promoter Score.

^n^CSAT: Customer Satisfaction Score.

^o^VAS-smiles: 5-point visual analogue scale represented by different emoticons used to answer the question “How was your therapy session today?”

^p^Robotic therapy data includes, for example, time of logging in and out, duration of sessions and breaks, number of task repetitions, correct answers, difficulty level of the exercises, and muscle tone data.

^q^Conventional therapy data includes the number and type of standard therapy sessions performed by the patient while participating in the clinical trial.

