### Data Analysis

Descriptive statistics will be used to describe the study population (eg, demographics, initial clinical scores, and changes in clinical scores, such as functional recovery), attendance and therapy dose in the unsupervised phase, user experience, and platform usability.

Normal distribution of the data will be checked with the Shapiro Wilk test. For each usability metric, a paired *t* test (normal distribution) or a paired samples Wilcoxon test (for data not normally distributed) will be performed to compare the data collected during the usability evaluation 1 and usability evaluation 2 sessions.

To evaluate the content of unsupervised therapy, 1-way repeated measures ANOVA or its nonparametric version (Friedman test) with post hoc tests will be run to compare intensity (average block intensity for each patient), performance, and ratio of effective therapy time to total session duration during supervised, minimally supervised, and unsupervised therapy. The same tests will be used to compare the answers to the VAS-smiles, a 5-point VAS represented by different emoticons, performed at the end of each therapy session during the 3 phases. For these comparisons, we expect therapy content and VAS-smiles not to vary significantly depending on the level of supervision, as ideally the absence of the therapist should not impact these outcomes. Patients who did not reach the unsupervised phase will be excluded from this analysis.

Linear mixed-effects models will be used to investigate parameters (eg, demographics and baseline data) possibly influencing the achieved dose of unsupervised therapy.

Relevant qualitative data will be summarized and reported accordingly.

Data analysis will be performed with MATLAB R2021b (MathWorks).

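### Because the device adapts difficulty to performance, similar task performance across phases is weak evidence that therapy content is unchanged without a therapist, and difficulty, though logged, is not compared

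*Protocol article*

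**What the plan says.** Secondary Outcomes names two measures first: "The difference in intensity (ie, number of task repetitions per minute) and task performance during supervised or minimally supervised therapy and unsupervised therapy". It gives their purpose: the difference "is used to evaluate if the content of the therapy varies when the therapist is no longer present". It then adds "A third metric to evaluate the difference in therapy content is the ratio of effective therapy time" to total session duration.

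Data Analysis compares "intensity (average block intensity for each patient), performance, and ratio of effective therapy time to total session duration" across the supervised, minimally supervised and unsupervised phases, by one-way repeated measures ANOVA or Friedman test. The stated expectation is no significant variation with the level of supervision. Patients who never reach the unsupervised phase are left out of this comparison.

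The section on the ReHapticKnob describes the exercises as "ensuring dynamic difficulty adaptation based on the user’s performance". It reports that a pilot in 5 patients showed the algorithms able "to automatically adapt the difficulty level of the exercises to keep therapy challenging". Nothing suggests that adaptation is switched off in any phase.

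Footnote p of Table 1 lists among the recorded robotic data "number of task repetitions, correct answers, difficulty level of the exercises, and muscle tone data". Difficulty is therefore available, but neither Secondary Outcomes nor Data Analysis includes it in the content comparison.

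**The concern.** A quantity that drives a feedback loop is a poor indicator of what the loop is responding to. Suppose a patient does less well once the therapist has left. If the device responds by easing the exercises, the success rate moves back towards its usual range and the change appears mainly in difficulty. The other two metrics do not close the gap, because a patient can keep the same repetition rate and the same share of active time on easier tasks.

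All three metrics could thus look alike across phases while the exercises became easier, which is a change of content in the ordinary sense. Since the plan expects no variation, such a result would agree with expectation and might not be questioned.

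**Working it through.** **No figure to reproduce.** The article gives no number for this comparison. The sample size, which sets the scale, does reproduce: 10/(1 − 0.20) = 12.5, rounded up to 13.

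**Inputs from the article.** Difficulty adapts to performance; the content metrics are intensity, performance and time ratio; difficulty and correct answers are both logged.

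**Inputs assumed.** Performance is the proportion of correct answers. Success follows P = expit(a − d), where a is ability, d is difficulty and expit(x) = 1/(1 + e^(−x)). The starting point is a − d = 1.1, so P = 0.750. Ability falls by 1 logit at the transition.

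**Step 1: the two limits and the range between them.** Let k be the share of the loss that the device absorbs by lowering difficulty. The change in success rate is expit(1.1 − (1 − k)) − expit(1.1).

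- k = 0 (no adaptation): 0.525 − 0.750 = −22.5 points.
- k = 0.5: 0.646 − 0.750 = −10.5 points (rounded from −0.1046).
- k = 0.9: 0.731 − 0.750 = −1.9 points.
- k = 1: 0.

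Any k above 0 damps the difference. The article does not allow k to be fixed.

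**Step 2: simulated rules.** 20 sessions, 4 blocks of 15 trials each, target 75% correct, the same 1-logit loss from session 11:

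| Assumed rule | Change in success rate |
|---|---|
| After every block, step 0.3 logit, no floor | about −1.6 points |
| Once per session, step 0.1 logit | about −12.5 points |
| Every block, floor 0.3 logit below start | about −15.2 points |
| Every block, starting level is the floor | about −19.3 points |
| No adaptation | −22.5 points |

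Under the first rule mean difficulty falls by about 0.92 logit, so nearly all of the loss shows there.

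**Step 3: a second fast rule at the trial's size.** Start at 70% correct, phases of 5, 5 and 10 sessions, 4 blocks of 10 trials, difficulty up 0.3 logit at 80% correct or more and down 0.3 below 60%. Results for 10 patients:

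- Loss of 0.5 logit: success falls from about 70% to 58% at fixed difficulty, but only from 64.6% to 63.4% with adaptation. Difficulty falls by 1.06 − 0.61 = 0.45 logit.
- Loss of 1.0 logit: from about 70% to 46% at fixed difficulty, but from 64.5% to 62.2% with adaptation. Difficulty falls by 1.51 − 0.61 = 0.90 logit.

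At an assumed 5% level, a 0.5-logit loss is detected on performance in 97% of runs at fixed difficulty and 37% with adaptation. The difficulty comparison detects it in 96%. For a 1.0-logit loss, performance with adaptation still detects it in 79% of runs (91% with 13 patients). With adaptation and no loss at all, the performance test rejects in 9% of runs (14% with 13 patients), because the first phase includes settling from the starting level. The adaptive detection rates on performance are therefore somewhat flattering.

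**Step 4: does difficulty alone solve it?** Add an assumed gain of 0.1 logit per session for recovery and practice to the first rule in Step 2. With no loss at the transition, mean difficulty rises by 0.98 logit between the two halves. With the 1-logit loss it changes by about +0.07. A comparison of phase means would then show almost no change in difficulty despite the loss. What remains visible is a break in the session-by-session course.

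**The case against.** A reader might infer that the device is designed to hold performance constant, so that a finding of no difference is built into the analysis. The article does not support this. It says that adaptation depends on performance and aims to keep therapy challenging; it gives no target success rate, step, update frequency or lowest level. Step 2 shows that damping can be nearly complete or slight, and Step 3 shows that even fast adaptation can leave a residual that reaches significance.

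Three further objections have force. First, performance is undefined, which a condensed article may fairly leave to the full protocol. A score that accounts for difficulty would largely meet the point. Secondly, the plan never proposes to judge content from performance alone; it names three metrics and also compares session ratings on the emoticon scale. Thirdly, difficulty should not replace performance. Patients enter within 6 weeks of stroke, receive full conventional therapy and pass through the phases in a fixed order, so difficulty would be expected to rise with time whatever the supervision.

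All of this limits the claim and shapes the remedy. What stands is that none of the named metrics records how hard the exercises were, on a device that changes exactly that in response to one of them.

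**Conclusion.** The point holds in a limited form. If performance is a success rate not weighted for difficulty, adaptation damps differences between phases, and similar performance is weak evidence that content is unchanged. For an assumed 1-logit loss, the visible change in success rate shrinks from 22.5 points to somewhere between about 1.6 and 19 points, depending on a rule the article does not state. The direction follows from the article's own description, provided difficulty is eased after poor performance; the size is indicative only. Intensity and time ratio do not fill the gap.

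Feasibility, dose and usability, the primary outcomes, are untouched. This is a worthwhile correction to one secondary comparison.

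**What to change.** Add difficulty level, within exercise and by session, to the content metrics in Secondary Outcomes and to the three-phase comparison in Data Analysis, and report it beside performance. State how performance is scored and whether the score accounts for difficulty. Rest any statement that content is maintained on difficulty, performance, intensity and time ratio together.

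Because phase order is fixed, plot difficulty and performance session by session, aligned on each patient's own transition (some transition a week later than others), and look for a break there instead of relying on phase means. State as a limit that recovery and practice cannot be separated from the change in supervision.

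The cost is one more variable in the analysis, with an interpretation that recovery restricts. The variable is already recorded and the article says analysis is still under way, so no new data are needed.
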